**PSMA PET result**

Negative or limited sites of disease

Uptake in prostate only

Uptake in pelvic nodes only

Uptake in pelvic nodes only

Limited extra-pelvic disease

Limited extra-pelvic disease

Extra pelvic disease

Extensive pelvic disease

**Possible PSMA PET/CT informed management**

Observation

Local salvage

Add pelvic node dissection or nodal radiotherapy

Hormone Therapy

Metastasectomy

Stereotactic ablative RT

Hormone Therapy

Chemotherapy

**Cohort 7.** [18F]DCFPyL as a problem-solving tool in patients with prostate cancer when confirmation of site of disease and/or disease extent may impact clinical management over and above the information provided by conventional imaging. All requests for inclusion in the Registry under Cohort 7 will be adjudicated by an expert panel at Cancer Care Ontario. The panel will consist of 3 physicians, including oncologists with prostate cancer expertise and radiologists/ nuclear medicine physicians with PET expertise. The panel will receive a summary of the patient's relevant clinical history, along with supporting documents. The panel will determine whether findings on PET may impact patient management. Decisions will be made by a majority. If the panel cannot reach a decision, input from a second panel of experts may be requested. The final decision of the expert panel will be shared with the study sponsor. In cases where PET is not approved by the panel, referring physician may appeal the decision after providing further clinical information or further explanation on how PET would impact patient management.

**HYPOTHESIS:**

In the setting of men treated with initial prostatectomy or primary radiotherapy experiencing biochemical failure on current management or have high risk disease at the time of initial surgery (node positive or persistently detectable PSA within 3 months post-surgery), PSMA PET will be able to detect men with limited number of sites of recurrent disease (4 or less) who can potentially be treated with metastases directed therapy with the intent of deferring or avoiding the need for systemic therapy interventions.

**OBJECTIVES****Primary Objective PREP**

To determine the proportion of men with sites of disease identified at the time of early biochemical failure in high risk disease in men treated with prostatectomy with or without adjuvant or salvage pelvic radiotherapy or hormone therapy as well as men treated with primary radiotherapy. This will be calculated as the number of men with at least 1 PSMA PET detected lesion that is scored as +5 (definitely malignant) or +4 (probably malignant) according to the local imaging read.

## **Primary Objective PREP Phase 2**

To determine the proportion of men with sites of disease identified at the time of early biochemical failure in high risk disease in men treated with prostatectomy with or without adjuvant or salvage pelvic radiotherapy or hormone therapy as well as men treated with primary radiotherapy when PSMA PET/CT is used without prescreening with conventional imaging. This will be calculated as the number of men with at least 1 PSMA PET detected lesion that is scored as +5 (definitely malignant) or +4 (probably malignant) according to the local imaging read.

## **Secondary Objectives**

1. Determine correlations between PSA levels at time of imaging and presence of disease detected on PSMA PET
2. Determine the proportion of men with oligometastatic recurrence (four or fewer sites including the prostate bed if positive) detected on PSMA PET as calculated by the number of men with 4 or fewer lesions identified as +5 (definitely malignant) or +4 (probably malignant) divided by the number of men with any number of +5 or +4 lesions detected.
3. Determine the number of men who have a change in management as indicated by responses from referring physicians on an impact questionnaire completed after PSMA PET scans are reported.
4. Determine the actual management delivered within 6 months by linkage to existing health information registries:
  - a. Delivery of radiotherapy (anatomic site, dose and fractionation) – Cancer Care Ontario
  - b. Biopsy of suspected recurrences (anatomic site, histology) – Provincial pathology database
  - c. Use of salvage lymph node dissections – CIHI
  - d. Use of salvage hormonal therapy/androgen deprivation
5. Compare PSA response at 6 months against PSA at the time of PSMA PET obtained through linkage to the Ontario Laboratory Information Services and correlate with actual management as determined in 4.
6. To compare the detection rates of PSMA PET/CT when conventional imaging is used as part of eligibility criteria (PREP) versus when conventional imaging is omitted (PREP Phase 2)

## **STUDY DESIGN**

The study will be conducted as a prospective registry. Seven cohorts of men will be examined: 1) men who are node positive or who have a persistently detectable PSA after initial radical prostatectomy, 2) men with biochemical failure after initial RP, 3) biochemical failure after initial RP and salvage RT, and 4) biochemical failure after initial RP with or without adjuvant/salvage RT who are currently on salvage hormone therapy, 5) men who have prior metastases directed treatment for oligometastatic disease with subsequent biochemical failure, 6) men with a rising PSA (Phoenix Criteria) following primary radiotherapy, 7) men whose clinical scenarios fall outside of cohorts 1-6 but where an independent adjudication process determines PSMA PET could provide clinically meaningful information. Participating centres will be responsible for submitting patient demographic data to establish eligibility upon review by the central PET registry, obtaining patient consent including consent for linkage of their data to existing provincial patient registries and providing results of the [18F]DCFPyL PET/CT on a standardized reporting form. Other patient related outcomes (interventions post PET/CT) will be assessed by linkage to existing patient registries to determine use of salvage surgical and radiotherapy procedures and use of hormone and systemic therapy. This registry study is expected to take 4 years to complete with an additional one year of follow-up to capture patient outcomes during which time additional patient enrollment on the individual cohorts will continue.

## **STUDY DESIGN – PHASE 2 REVISION**

During Phase I of the PREP protocol, all patients were required to have conventional imaging (computed tomography and bone scan) either negative or demonstrating oligometastatic disease. Based on an analysis of the first 400 patients accrued, the majority of patients (76%) had negative conventional imaging, with 24% had oligometastatic disease. Overall PSMA PET/CT detection rates of new lesions were similar among patients with negative conventional imaging (59%) versus oligometastatic disease on conventional imaging (63%). There were 12% of patients who had extensive disease on subsequent PSMA PET/CT with the rest of patients having negative scans or oligometastatic disease. Of these patients half (6%) had negative conventional imaging and half had oligometastatic

disease on conventional imaging (patients who had extensive metastatic disease on conventional imaging were not eligible for participation in PREP). Given these findings, it would appear that conventional imaging is not providing additional value in terms of overall staging compared to PSMA PET/CT alone, although this conclusion is limited somewhat by the fact that patients with extensive disease were excluded from participation from the first Phase of PSMA PREP. Given the historical data suggesting low rates of positive conventional imaging at PSA levels (<10 ng/ml) where actionable (locally recurrent or oligometastatic) disease is most likely to be found (27, 28) it is reasonable to hypothesize that omission of conventional imaging as criteria for PSMA PET/CT should not materially affect the performance of the test. Omission of conventional imaging would save costs and also improve the efficiency of evaluating men as currently waits for conventional imaging can add weeks to months to the waiting time for accessing PSMA PET/CT as part of PREP. To investigate the hypothesis that conventional imaging is not adding to the information provided by PSMA PET/CT alone, PREP Phase 2 will retain the same study design as Phase I but will remove bone scan and computed tomography as criteria for entry into the study except for those patients with higher PSA (>10 ng/ml). Identical cohort sizes will be accrued in Phase 2 to permit comparison of detection rates with similar confidence intervals with and without conventional imaging. Transition to PREP Phase 2 will occur when overall accrual to PREP has exceeded 80% of target.

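### Phase 2 says it will test whether conventional imaging adds information to PSMA PET/CT, but Objective 6 compares only PET-positive rates between phases and cannot show disease that PET misses

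*Protocol*

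**What the plan says.** The section STUDY DESIGN – PHASE 2 REVISION reports on the first 400 men: "the majority of patients (76%) had negative conventional imaging, with 24% had oligometastatic disease". PET detection of new lesions was 59% after negative and 63% after oligometastatic conventional imaging, which the protocol calls similar. On extent: "There were 12% of patients who had extensive disease on subsequent PSMA PET/CT", and "Of these patients half (6%) had negative conventional imaging and half had oligometastatic" disease. From these findings it concludes that "it would appear that conventional imaging is not providing additional value in terms of overall staging compared to PSMA PET/CT alone". It adds one limitation, that men with extensive disease on conventional imaging could not enter Phase 1, and it also cites historical data on low yield at PSA below 10 ng/ml.

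Two hypotheses follow in the same section. One is that dropping conventional imaging leaves PET performance essentially unchanged. The other is stated as the purpose of the phase: "To investigate the hypothesis that conventional imaging is not adding to the information provided by PSMA PET/CT alone".

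The phases are compared by Objective 6 (Secondary Objectives, under both OBJECTIVES and OUTCOMES ASSESSMENT), which contrasts PET detection rates with and without conventional imaging as an entry criterion. Under the primary objectives, detection means at least one lesion scored +4 or +5 on the local read.

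**The concern.** The second hypothesis is about information: does conventional imaging show anything that PET does not? Objective 6 measures how often PET is positive, which is a different quantity. In Phase 2, men with PSA of 10 ng/ml or below need no conventional imaging at all, so for most of the intended question Phase 2 cannot supply the missing data. Phase 1 required both tests.

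At stake is the interpretation. Similar detection rates in the two phases could be reported as support for no added information, when no analysis named in the protocol looks at men whose disease appeared only on conventional imaging. The Phase 1 figures in the rationale have the same gap.

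**Working it through.** **Inputs** (all from STUDY DESIGN – PHASE 2 REVISION): 400 men; 76% conventional-negative; 24% oligometastatic; 12% extensive on PET, half from each group; new-lesion detection 59% v 63%.

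**1. Reproduce the protocol's figure.** 0.76 × 400 = 304; 0.24 × 400 = 96; 0.12 × 400 = 48; 48 / 2 = 24; 24 / 400 = 6%. The stated 6% is right as a share of all men.

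**2. The same men by imaging group.**

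| Conventional result | Extensive on PET | Rate | Exact 95% CI |
|---|---|---|---|
| Negative | 24/304 | 7.9% | 5.1 to 11.5% |
| Oligometastatic | 24/96 | 25.0% | 16.7 to 34.9% |

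- Ratio: 0.250 / 0.0789 = 3.17. The SE of its log is √(1/24 − 1/96 + 1/24 − 1/304) = 0.264, so the 95% CI is 1.89 to 5.31.
- Difference: 17.1 points (95% CI 7.9 to 26.3).
- With no association, 48 cases would split 0.76 × 48 = 36.5 and 0.24 × 48 = 11.5, not 24 and 24.
- Over all counts consistent with the rounded percentages, the ratio stays between 2.7 and 3.6.

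**3. Detection of new lesions.** 63% − 59% = 4 points. SE = √(0.63 × 0.37/96 + 0.59 × 0.41/304) = 0.0568. The 95% CI is 4 ± 1.96 × 5.68, about -7 to +15 points.

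**4. What Objective 6 can see.** Cross-classify each man:

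| | PET positive | PET negative |
|---|---|---|
| Conventional positive | a | c |
| Conventional negative | b | d |

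The PET detection rate is (a + b)/N. Disease found only by conventional imaging lies in c. Moving men between c and d leaves the detection rate unchanged, so no comparison of detection rates identifies c.

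The protocol's figures only bound it. Of the 96 conventional-positive men, 37% had no new PET lesion: 0.37 × 96 = 35.5, about 36. The text does not say whether PET confirmed the known lesions in these men or was negative. So c could be 0 to about 36, that is 0 to 37% of conventional-positive men, or 0 to 8.9% of all men (35.5/400).

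**5. Comparability of the phases.** Phase 1 excludes more than four unequivocal sites on conventional imaging (except in Cohort 7). Phase 2 has no such exclusion, and its remaining conventional-imaging criterion applies only when PSA exceeds 10 ng/ml. Men with extensive disease and lower PSA can therefore enter Phase 2 but not Phase 1, so a change, or an absence of change, in detection may reflect case mix.

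**6. What a within-man table would give.** If c = 0 of the 96 men already analysed, the exact 95% upper limit is 1 − 0.025^(1/96) = 3.8%. If the 24% share persists to the switch at 80% of 1,535 (0.8 × 1,535 = 1,228; 0.24 × 1,228 ≈ 295), the limit for c = 0 is 1 − 0.025^(1/295) = 1.2%. If 15 of 295 (5%, an illustrative value) are discordant, the exact CI is 2.9 to 8.2%.

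**The case against.** The rationale is more careful than a quick reading suggests. It draws on the detection rates and historical data as well as the split of extensive cases, is worded tentatively, states a limitation, and keeps conventional imaging as an entry requirement at PSA above 10 ng/ml. Objective 6 also fits the other hypothesis in that section, that PET performance holds up without conventional imaging. All of this stands.

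A reader might infer that the 6% has the wrong denominator. It does not: it is a correct share of all 400 men. What it cannot do is show that extent is unrelated to the conventional result.

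A reader might also infer that 7.9% v 25.0% refutes the protocol's conclusion. It does not. PET itself found all 48 extensive cases, so the contrast shows that conventional imaging correlates with extent on PET, not that it contributes anything once PET is done.

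The proposed table has limits. Biopsy is encouraged but not mandated (Confirmatory Biopsy), so c mixes PET misses with conventional false positives. It does not capture men positive on both tests at different sites. Conventional imaging may be up to 3 months from registration and PET up to 6 months after it, so the two may be as much as 9 months apart. These limits affect how c is read; they do not make a detection-rate comparison a substitute for it.

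Finally, an SAP, which is not at hand, may add cross-tabulations. The point here is narrower: the protocol itself states the hypothesis and the comparison, and they do not match.

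**Conclusion.** The point holds as a mismatch between a stated hypothesis and its linked analysis. Objective 6 cannot address whether conventional imaging adds information to PET, and the Phase 1 figures cited leave that open: a 4-point detection difference with a CI of about -7 to +15, and an extensive-disease split that is uneven by group (7.9% v 25.0%) but silent on added value over PET. The quantity that bears on the question is bounded by the reported figures only between 0 and about 36 of 96 conventional-positive men.

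This rests on reading the percentages as shares of 400, as the half-of-12% wording implies, and on counting any man with a new PET lesion as PET-positive. The projection to 295 men also assumes that the 24% share persists. The documents do not support saying that the rationale is miscalculated, that it rests on the split alone, or that conventional imaging has been shown to add to PET. The detection-rate endpoints themselves are unaffected.

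**What to change.** - Add a within-man Phase 1 table of conventional result (negative, oligometastatic, with a stated place for equivocal scans) by PET result (negative, oligometastatic, extensive). Report the conventional-positive, PET-negative proportion with an exact 95% CI, overall and for PSA 10 ng/ml or below. Name this as the evidence for the no-added-information hypothesis.
- Describe the discordant cell as an upper bound on men with true conventional-positive disease and a wholly negative PET. State that it omits site-level discordance, and use the pathology linkage in Objective 4b where biopsy exists.
- Keep Objective 6 for the separate hypothesis that PET performance is not materially changed, and note the case-mix difference between phases.
- In the Phase 2 rationale, give the group rates (24/304 and 24/96) beside the 6%, say that they show neither presence nor absence of added value, and soften the conclusion accordingly.

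The cost is one table and some rewording. Conventional imaging was required at Phase 1 entry and PSA is on the eligibility form, so no new data are needed. The downside is that the rationale reads less favourably.

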### **Exclusion Criteria**

1. Prostate cancer with significant sarcomatoid or spindle cell or neuroendocrine small cell components
2. Extensive metastatic disease on conventional restaging (>4 sites unequivocally positive for disease). Unless PET/CT requested as part of Cohort 7.
3. Prior PSMA PET scan within 6 months of enrollment
4. Patient cannot lie still for at least 60 minutes or comply with imaging
5. Patients falling outside of Cohorts 1-6 where independent adjudication by CCO does not support participation in the Registry

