### **Inclusion Criteria**

1. Written informed consent obtained
2. Male, Age  $\geq 18$  years
3. Prior primary treatment for prostate cancer with curative intent such as radical prostatectomy **or** radiotherapy for localized prostate cancer. Unless PET/CT requested as part of Cohort 7.
4. Suspected persistent or recurrent disease defined as one of the following:
  - a. High risk disease at the time of radical prostatectomy characterized by pathologically involved node(s) **or** persistently detectable PSA ( $>0.1\text{ng/ml}$ ) within 3 months post-surgery
  - b. Primary treatment for prostate cancer and biochemical failure (BF) with current management according to the following:
    - i. Following primary radical prostatectomy, BF is defined as rising PSA on at least 2 occasions measured at least 1 month apart and with the most recent PSA measured at  $>0.1\text{ ng/ml}$
    - ii. Following primary radiotherapy for localized disease, BF is defined according to the Phoenix Definition, which is rising PSA on at least 2 occasions measured at least 1 month apart and with the most recent PSA measured greater than the nadir PSA +  $2.0\text{ ng/ml}$ .

Unless PET/CT requested as part of Cohort 7.

5. Patient scenario falls into one of the 7 pre-defined cohorts. When patient scenario falls outside cohorts 1-6 participation in the Registry must be approved through the established CCO adjudication process for cohort 7.
6. Karnofsky performance status 70 or better (ECOG 0, 1)
7. If PSA  $>10\text{ ng/ml}$ , conventional imaging consisting of bone scan and abdominal-pelvic CT scan performed within 3 months of registration that is either equivocal, negative (no lesions) or positive for oligometastatic disease (4 or fewer unequivocal lesions identified). Registration is defined as Form A: Eligibility is complete.

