## **Secondary Objectives**

1. The likelihood of disease detected on PSMA PET will be correlated with absolute PSA level at the time of PSMA PET as supplied on the eligibility form.
2. The proportion of men with oligometastatic recurrence (four or fewer sites including the prostate bed if positive) detected on PSMA PET will be calculated as the number of men with 4 or fewer lesions identified as +5 (definitely malignant) or +4 (probably malignant) divided by the number of men with any number of +5 or +4 lesions detected.
3. The number of men who have a change in management will be determined by comparison of the management questionnaire obtained at the time of registration to the repeat questionnaire performed after the PSMA PET scans are reported.
4. Actual management within 6 months will be determined through linkage to existing health information registries and will include:
  - a. Delivery of radiotherapy (anatomic site, dose and fractionation) – Cancer Care Ontario
  - b. Biopsy of suspected recurrences (anatomic site, histology) – Provincial pathology database
  - c. Use of salvage lymph node dissections – CIHI
  - d. Use of salvage hormonal therapy/androgen deprivation
5. PSA response will be examined by comparing 6 month PSA against PSA at the time of PSMA PET through the Ontario Laboratory Information Services and correlated with actual management as determined in 4.
6. Comparison of the detection rates of PSMA PET/CT when conventional imaging is used as part of eligibility criteria (PREP) versus when conventional imaging is omitted (PREP Phase 2)

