## **STATISTICAL CONSIDERATIONS**

### *Statistical Analyses*

Descriptive statistics will be used to summarize patient, tumour and treatment characteristics, along with endpoints. The primary endpoint will be described using proportions, along with a 95% exact confidence interval, and tested using an exact test of proportions. Secondary endpoints will be summarized using descriptive statistics, along with confidence intervals as appropriate. All tests and confidence intervals will be two-sided and statistical significance will be defined at the  $\alpha=0.05$  level. No statistical adjustments will be performed for multiple testing; however, appropriate caution will be taken when inferring results from this study due to the fact that multiple tests will be

performed. Given the sample size, all tests and confidence intervals will be based on exact or non-parametric methods.

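### The Phase 1 versus Phase 2 detection comparison mixes a change in patient selection with the imaging question, and should be restricted, adjusted and extended to disease extent

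*Protocol*

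**What the plan says.** **The question.** Under Study Design – Phase 2 Revision, the protocol puts forward as a hypothesis that "omission of conventional imaging as criteria for PSMA PET/CT should not materially affect the performance of the test". On size it says "Identical cohort sizes will be accrued in Phase 2 to permit comparison of detection rates with similar confidence intervals with and without conventional imaging". Secondary objective 6 reads "To compare the detection rates of PSMA PET/CT when conventional imaging is used as part of eligibility criteria (PREP) versus when conventional imaging is omitted", and Outcomes Assessment repeats it. Detection means at least one PET lesion scored +4 or +5 on the local read. Phase 2 follows Phase 1, once accrual passes 80% of target.

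**Who enters each phase.** Phase 1 requires bone scan and CT from every man, and its exclusion item 2 is "Extensive metastatic disease on conventional restaging (>4 sites unequivocally positive for disease", waived for Cohort 7. Phase 2 has no such exclusion. Its inclusion item 7 still asks for "conventional imaging consisting of bone scan and abdominal-pelvic CT scan performed within 3 months of registration", showing no more than four unequivocal lesions, but only when PSA is above 10 ng/ml.

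**Analysis.** Statistical Analyses sets two-sided tests at 0.05, summarises secondary endpoints descriptively with confidence intervals where appropriate, and adds: "Given the sample size, all tests and confidence intervals will be based on exact or non-parametric methods". No margin is given for a material effect.

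**Interim data.** Of the first 400 men, 76% had negative and 24% oligometastatic conventional imaging. PET showed extensive disease in 12%: "Of these patients half (6%) had negative conventional imaging and half had oligometastatic" disease. The protocol concedes that excluding extensive disease limits its interim conclusion to some degree.

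**The concern.** Objective 6 is the comparison that tests the reason for Phase 2. A difference between the phases, or the lack of one, should therefore reflect the omission of conventional imaging. Three features get in the way.

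- Part of the Phase 2 group is prescreened exactly as in Phase 1, which pulls the contrast towards no difference.
- In the rest, the entry rule changed in a direction that raises Phase 2 detection even if the test performs the same.
- The compared endpoint records whether any lesion is seen, not how much disease there is, while the dropped criterion acts on extent.

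At stake is a finding of similar or better detection in Phase 2 that arises partly from who was admitted, used to support dropping an imaging step.

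**Working it through.** **1. The plan's own size.** Sample Size Revision, Cohorts 2, 3, 6 assumes 60% detection and ±5 points:

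n = 1.96² × 0.6 × 0.4 / 0.05² = 368.8, so 369. This reproduces.

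**2. The same size used for a difference.** Half-width = 1.96 × √(2 × 0.24 / n).

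| Men per phase | One rate | Difference |
|---|---|---|
| 369 | ±5.0 | ±7.1 points |
| 56 | ±12.8 | ±18.1 points |

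Power of a two-sided 0.05 test (normal approximation), starting from 60%:

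| Men per phase | True fall of 5 points | True fall of 10 points |
|---|---|---|
| 56 | 8% | 18% |
| 369 | 28% | 78% |
| 1083 (Cohorts 2, 3 and 6 pooled) | about 65% | over 99% |

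The 1083 is 425 × 0.85 = 361 evaluable per cohort, times 3.

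**3. Dilution by PSA above 10.** If a share w of men in each phase has PSA above 10, a true difference d at PSA of 10 or below appears as (1 − w) × d. The documents do not give w. With w of 10% or 20% (assumption), a 5-point loss appears as 4.5 or 4.0 points.

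**4. Selection at PSA of 10 or below.** Let f be the share of Phase 2 men whom Phase 1 would have excluded for more than four conventional lesions, and q the share of these who are PET positive. The Phase 2 rate with no change in the test is 0.60 × (1 − f) + f × q. The true fall that would be hidden is 0.60 − (0.60 − f × q)/(1 − f). Neither f nor q is in the documents; q is taken as 90% to 100%.

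| f | Phase 2 rate | Fall that is hidden (points) |
|---|---|---|
| 2% | 60.6–60.8% | 0.6–0.8 |
| 5% | 61.5–62.0% | 1.6–2.1 |
| 10% | 63.0–64.0% | 3.3–4.4 |
| 15% | 64.5–66.0% | 5.3–7.1 |

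**5. Case mix.** The meta-analysis cited in the sample size revision gives detection of 0.48 at PSA 0.2–0.49 and 0.97 above 2. If 10% of men moved from the lowest to the highest band between phases, the rate would change by 0.10 × (0.97 − 0.48) = 4.9 points, about the precision planned for one rate.

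**6. Disease extent in the Phase 1 data.** Of 400 men, 304 (76%) had negative and 96 (24%) oligometastatic conventional imaging. Extensive PET disease in 12% is 48 men, half in each group:

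- negative: 24/304 = 7.9%
- oligometastatic: 24/96 = 25.0%

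The difference is 17.1 points (95% CI 8 to 26; Fisher p about 0.00004). Rounding of the 6% moves these only to 5.5/76–6.5/76 = 7.2–8.6% and 5.5/24–6.5/24 = 23–27%. The conventional result was thus related to extent on PET, so extent should be compared when that result no longer governs entry.

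**The case against.** Much can be said for the plan.

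- Objective 6 is worded as a comparison of eligibility policies, so some change in the men admitted belongs to the question. This stands, but a policy comparison does not by itself answer the stated hypothesis about test performance.
- The shares in step 4 are not documented, and large ones may be unlikely. The sample size section puts all conventional detection below 10%, although 24% of the first 400 men had oligometastatic disease. The size of the effect is therefore uncertain, while its direction follows if these men are PET positive more often than the rest.
- The PSA above 10 exception is stated openly, and the Phase 2 objective under Outcomes Assessment speaks only of routine prescreening. Openness does not remove the dilution.
- Secondary objective 2 already collects the share of positive men with four or fewer lesions. It is not named as a phase comparison.

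A reader might infer more than the text supports:

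- **That 59% versus 63% shows the endpoint to be insensitive.** Those are rates of new lesions by conventional result, not the protocol's endpoint. Likewise, 7.9% versus 25% is a contrast within Phase 1, not between phases.
- **That adjustment is ruled out.** Stratified exact methods meet the exact or non-parametric rule, and the statement about not adjusting concerns multiple testing. The SAP, which is not shown, may stratify by PSA.
- **That a non-significant test will be taken as equivalence.** No test is named for objective 6, and intervals alone would be consistent with the protocol.
- **That the comparison has little chance of showing a loss.** This holds for the small cohorts, but not for Cohorts 2, 3 and 6 pooled.

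**Conclusion.** The point holds as a recommended improvement. As defined, objective 6 is diluted by men with PSA above 10 and, at PSA of 10 or below, is open to a rise in Phase 2 detection that comes from selection. At a 60% rate the rise is about 2 points for each 5% of newly admissible men, if all are PET positive; both the share and the positivity are assumptions. Any-lesion detection alone does not show whether disease extent shifts. Equal cohort sizes secure similar precision for each rate, but only ±7 points (369 per phase) or ±18 points (56 per phase) for the difference.

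It would go too far to say that the protocol claims equivalence: it states a hypothesis and concedes a limitation of its interim data. The Phase 2 primary objective is a proportion within one phase and does not depend on this comparison, so the change is not a condition for the trial to proceed.

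**What to change.** Revise secondary objective 6 in both places where it appears:

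1. Restrict the main phase comparison to men with PSA of 10 ng/ml or below in both phases.
2. Among all scanned men in that group, compare the proportions with 0, 1–4 and more than 4 PET lesions scored +4 or +5, as well as any detection.
3. Estimate the phase difference stratified by, or adjusted for, cohort and PSA at imaging. State under Statistical Analyses that the exact or non-parametric rule does not bar this.
4. Report the difference with its 95% interval, pooled over Cohorts 2, 3 and 6, and treat Cohorts 1, 4, 5 and 7 as descriptive.
5. Describe performance as not materially affected only if that interval excludes a loss fixed in advance by the sponsor.

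Restriction to PSA of 10 or below removes the dilution. It does not remove the newly admissible men, so the three-level result is needed to show where a change lies. Eligibility need not change. An analysis limited to men with four or fewer PET lesions is not advised, because it conditions on the outcome.

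**Cost.** Wording only: PSA is on the eligibility form and the number of lesions is in the PET report. Precision falls as men with PSA above 10 leave this comparison. For a purely illustrative 7-point margin, 60% in both phases and one-sided 2.5%, unadjusted power with 1083 per phase is Φ(0.07/√(0.48/1083) − 1.96) = about 91%. If 20% leave (assumption), 866 per phase remain and power is about 84%.
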